### Overview of study design and study population

This study adheres to the principles of the Declaration of Helsinki and has been approved by the NIH Clinical Center Deputy Ethics Counselor and the National Heart, Lung, and Blood Institute (NHLBI) Institutional Review Board (12-CC-0211). Written informed consent will be obtained from all participants at the NIH Clinical Center prior to undergoing any testing or treatment described in this protocol. Most eligible patients will be referred from Pulmonary Hypertension Specialty Clinics. At the time of enrollment, each patient will be asked to identify a primary responsible licensed practitioner who will be notified of the patient’s enrollment and made aware of the potential development of adverse study drug effects (such as hyperkalemia and renal insufficiency) during the course of the trial. If a patient does not have a physician with expertise in PH, then they will either be referred to a physician with such expertise or they will be provided ‘standard of care’ therapy at the NIH. Eligibility will be based on information obtained from our Natural History Study and from any additional information provided by the referring physician. Participants must be at least 18 years of age and must be able to provide informed, written consent for participation in this study. There is no exclusion based on race or gender. Women of childbearing potential must agree to use adequate contraception prior to and for the duration of study participation.

Eligible individuals are patients with PAH (that is, Group 1 PH, Table 1) without clinical evidence of RV failure receiving either no medical therapy or stable medical therapy for at least the past 4 weeks (defined as no new PAH-specific therapy, no change in the dose of current PAH-specific therapy and no change in NYHA/WHO functional classification). The following parameters on right heart catheterization are required to meet the hemodynamic definition of PAH: mean pulmonary artery pressure of >25 mmHg at rest, pulmonary capillary wedge pressure of ≤15 mmHg (or LV end-diastolic pressure ≤12 mmHg) and pulmonary vascular resistance of >3 Wood units (240 dyn ⋅s ⋅cm^-5^). If clinically indicated at the time of enrollment, then a right heart catheterization will be performed at the NIH Clinical Center upon study entry. Exclusion criteria are as follows:

1. Patients with WHO Group 1 PH and evidence of right heart failure as defined by:

a. NYHA/WHO class IV symptoms

AND

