b. Echocardiographic evidence of severe RV dysfunction

AND

c. Clinical signs which may include, but are not limited to elevated jugular venous pressure, ascites, and lower extremity edema

2. Patients with WHO Group 1 PH and a prior diagnosis of cirrhosis with portal hypertension as evidenced by a history of ascites, hepatic encephalopathy and/or varices prior to enrollment.

3. Patients with WHO Group 1 PH and evidence of active infection. (Patients with HIV infection and two consecutive viral loads of <500 on their most recent determinations in the past 12 months will be considered to have inactive infection.)

4. Patients with WHO Group 1 PH who have taken spironolactone or eplerenone within the last 30 days.

5. Known or suspected allergy to spironolactone.

6. Pregnant or breastfeeding women.

7. Age <18 years.

8. Inability to provide informed written consent for participation in the study.

9. Chronic kidney disease defined as estimated glomerular filtration rate (eGFR) of <50 mL/min/1.73 m^2^ of body surface area. (eGFR will be calculated using the isotope dilution mass spectrometry-traceable Modification of Diet in Renal Disease Study equation and corrected for body surface area as follows: eGFR = 175 × (serum creatinine in mg/dL)^-1.154^ × (age in years)^-0.203^ × [1.212 if African-American] × [0.742 if female].)

10.  Serum potassium at the time of enrollment of >5 mEq/L or current use of potassium-sparing diuretics, angiotensin-converting enzyme (ACE) inhibitors, angiotensin II receptor blockers or drospirenone-containing oral contraceptives.

All participants will undergo baseline testing under our Natural History protocol and serial (12 and 24 weeks) testing under this protocol according to the schedules outlined in Additional file 1: Figure S1 (all time points are approximations, ±7 days). Following each interval assessment period (baseline, 12 and 24 weeks), patients will be discharged home under the care of their referring and/or primary physicians. During the study, participants are permitted to have other medications, including PAH-specific therapies, adjusted by their primary physician as clinically necessary.

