### Monitoring of participants and criteria for withdrawal from study

#### Spironolactone treatment

As a safeguard, at the time of enrollment each patient will be asked to identify a primary responsible physician who will be notified of the patient’s enrollment and, therefore, will be aware of the potential development of hyperkalemia or renal insufficiency during the course of the study. Serum potassium, blood urea nitrogen and creatinine will be measured one week after initiating therapy or a dose increase and then serially thereafter according to the pre-specified schedule (Figure 1 and Additional file 1: Figure S1). For laboratory monitoring of serum potassium, blood urea nitrogen and creatinine on day 7, week 6, week 9, week 16 and week 20 (±7 days), participants will be given laboratory requisition slips for sample collection at an outside facility near their home (Additional file 1: Figure S1). Participants will be instructed to have their samples drawn within 7 days of the specified time point. Those participants who wish to return to the NIH Clinical Center to have these samples drawn may do so instead of going to an outside facility. For laboratory monitoring of serum potassium, blood urea nitrogen and creatinine at week 12 and week 24, samples will be collected along with other research samples at the time of the NIH Clinical Center visit (Additional file 1: Figure S1). In the event that specimens are reported as hemolyzed, participants will be instructed to repeat their sample draw within 7 days of their previous sample. In the event that any scheduled laboratory monitoring is delayed for >7 days, participants will be instructed to stop the study drug and will be removed from the protocol.

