### Individual participant stopping rules

PAH is a progressive disease and therefore clinical worsening may occur in participants during the protocol, irrespective of their treatment group assignment. Individual stopping rules for participants enrolled in the protocol include:

1. If a participant develops clinical evidence of right heart failure (which may include but is not limited to elevated jugular venous pressure, ascites and lower extremity edema) as determined by the patient’s primary physician or the investigators, then the participant will be removed from the protocol and treated for decompensated right heart failure according to standard of care.

2. If a participant deteriorates clinically, even in the absence of overt right heart failure, and the primary treating physician or the investigators feel that the addition of a MR antagonist such as spironolactone or eplerenone is clinically indicated then the participant will be removed from the study.

3. If a participant has more than one episode of serious hyperkalemia (potassium ≥5.3 mEq/L) or one episode of severe hyperkalemia (potassium ≥6.0 mEq/L), the study drug will be discontinued and the participant will be removed from the protocol.

4. If a participant develops renal insufficiency (rise in serum creatinine >50% of baseline) while on protocol, then the study drug will be discontinued and the participant will be removed from the protocol.

5. In the event that testing for serum potassium, blood urea nitrogen and creatinine is delayed for >7 days, the participant will be instructed to stop the study drug and will be removed from the protocol.

6. In any participant with a serum potassium level ≥ 5.3 mEq/L, a delay in laboratory monitoring longer than 48 hours from the specified time frame will result in removal from the protocol.

7. If while on study drug a participant develops significant breast pain or gynecomastia then the study drug will be discontinued and the participant will be removed from the protocol.

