#### Participation of pregnant women

Because of potential adverse effects on the fetus, pregnant participants will be excluded from the study. In addition, women of childbearing potential must agree to use adequate contraception (hormonal, barrier method of birth control, or abstinence) prior to and for the duration of study participation. Female participants with childbearing potential will be regularly assessed throughout the study. In the event of a positive pregnancy test, the participant will be immediately informed of this result, the study drug will be discontinued, and the participant will be removed from the study.

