### Risks and discomforts

#### Risks associated with spironolactone therapy

The most significant risks associated with spironolactone therapy include hyperkalemia, renal insufficiency, hypovolemia and gynecomastia with or without breast pain. In a large trial of patients with NYHA class III and IV LV heart failure (the mean dose of spironolactone was 26 mg and dose titration up to 50 mg daily), the incidence of severe hyperkalemia (>6 mEq/L) was not significantly different between the spironolactone treatment group (2%) and placebo (1%) but the median potassium concentration did increase by 0.30 mmol/L in the spironolactone-treated group [15]. The median creatinine concentration also increased (0.05 to 0.10 mg/dL) in the spironolactone-treated group. The risk of hyperkalemia while on spironolactone therapy is increased in the presence of renal insufficiency, concurrent use of ACE inhibitors or angiotensin receptor blockers, potassium-sparing diuretics or NSAIDs [66]. Precautions that will be taken include: participants will be counseled to avoid foods high in potassium and to avoid concurrent use of NSAIDs; patients taking ACE inhibitors, angiotensin receptor blockers, or potassium-sparing diuretics will be excluded from the study; participants will undergo frequent monitoring of serum potassium, creatinine and blood urea nitrogen; cessation of the study drug when serum potassium ≥6 mEq/L or when it remains ≥5.3 mEq/L on two occasions; and cessation of the study drug when creatinine increases by >50% of baseline value.

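### Drugs barred at entry for hyperkalemia risk are not excepted from the on-study permission to adjust medication, and starting one prompts no trial potassium draw (minor safety point)

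*Protocol article*

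**What the plan says.** All references are to the protocol article.

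- **Entry.** In *Overview of study design and study population*, exclusion criterion 10 bars "current use of potassium-sparing diuretics, angiotensin-converting enzyme (ACE) inhibitors, angiotensin II receptor blockers or drospirenone-containing oral contraceptives". The criterion is worded as use at enrollment.
- **During treatment.** The same section closes with: "During the study, participants are permitted to have other medications, including PAH-specific therapies, adjusted by their primary physician as clinically necessary".
- **Contraception.** *Participation of pregnant women* requires "adequate contraception (hormonal, barrier method of birth control, or abstinence) prior to and for the duration of study participation". Drospirenone products are not excepted here.
- **Risk.** *Risks associated with spironolactone therapy* says hyperkalemia is more likely with renal insufficiency or "concurrent use of ACE inhibitors or angiotensin receptor blockers, potassium-sparing diuretics or NSAIDs". Its precautions include excluding patients on the first three classes and counseling participants against NSAIDs.
- **Monitoring.** Under *Spironolactone treatment*: "Serum potassium, blood urea nitrogen and creatinine will be measured one week after initiating therapy or a dose increase". After that, draws follow a calendar: "on day 7, week 6, week 9, week 16 and week 20" at outside facilities, plus weeks 12 and 24 on site. Repeat draws follow a hemolyzed sample or a potassium of 5.3 mEq/L or more.
- **Removal.** In *Individual participant stopping rules*, rule 1 covers right heart failure: "then the participant will be removed from the protocol and treated for decompensated right heart failure according to standard of care". Rule 2 removes anyone who deteriorates and is judged to need a mineralocorticoid receptor antagonist.
- **Notice.** The primary practitioner is told of the enrollment and "made aware of the potential development of adverse study drug effects (such as hyperkalemia and renal insufficiency) during the course of the trial".

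**The concern.** The entry exclusion keeps a known interaction out of the trial on day 0. The on-study sentence then gives a physician outside the trial a general permission that does not repeat it. Someone acting within that permission could start, for example, an ACE inhibitor or angiotensin receptor blocker for systemic hypertension, or change a participant to a drospirenone contraceptive. The first of these is a combination that the protocol itself names as a hyperkalemia risk.

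Elsewhere the article does set on-study rules for interacting drugs: NSAIDs are counseled against, potassium supplements are addressed, and a need for a mineralocorticoid receptor antagonist leads to removal. The other classes in criterion 10 have no such rule. What is at stake is participant safety, through later detection of a rise in potassium.

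**Working it through.** **Step 1: what follows the start of a barred drug.**

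| Reason for the start | Removal rule | Extra trial draw |
|---|---|---|
| Right heart failure | Rule 1 | Not needed, participant leaves |
| Mineralocorticoid receptor antagonist judged necessary after deterioration | Rule 2 | Not needed, participant leaves |
| ACE inhibitor, angiotensin receptor blocker, other potassium-sparing diuretic or drospirenone contraceptive for another reason | None stated | None stated |

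The gap is the third row. The word adjusted in the permission reasonably includes starting a drug, since *Study endpoints* counts a new PAH drug or a new diuretic as an on-study event.

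**Step 2: wait to the next scheduled trial draw.** The protocol gives no figure for this, so there is none to reproduce.

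Inputs: scheduled draws at weeks 1, 6, 9, 12, 16, 20 and 24. Gaps after week 1: 5, 3, 3, 4, 4 and 4 weeks, total 23. Assumption: the start time is uniform over weeks 1 to 24.

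A start falls in a given gap with probability gap/total and then waits half that gap on average, so

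mean wait = Σ(gap²) / (2 × total) = (25 + 9 + 9 + 16 + 16 + 16) / (2 × 23) = 91/46 = 1.98 weeks.

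Share of start dates with a longer wait:

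- more than 1 week: (4 + 2 + 2 + 3 + 3 + 3)/23 = 17/23 = 74%
- more than 2 weeks: (3 + 1 + 1 + 2 + 2 + 2)/23 = 11/23 = 48%
- more than 3 weeks: (2 + 0 + 0 + 1 + 1 + 1)/23 = 5/23 = 22%

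The longest nominal wait is 5 weeks, between weeks 1 and 6.

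**Step 3: sensitivity.** Counting from day 0 adds a 1-week gap: 92/48 = 1.92 weeks. A simulation that moved each draw at random within its ±7-day window gave about 2.0 weeks. At the extremes of the windows (the week 1 draw taken at day 0, the week 6 draw at week 7) the longest gap is 7 weeks.

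**Step 4: the dose step.** *Treatment delivery* ties the increase to 50 mg to the week 6 laboratory result, and the Figure 1 caption places it at 8 weeks. A drug started between weeks 6 and 8 is first reflected in the week 9 draw, 1 to 3 weeks later, after the dose has doubled. This window is 2/23 = 9% of start dates.

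**The case against.** **The article is condensed.** A list of restricted concomitant drugs may well stand in the full protocol, and the monitoring figures are not shown. This is a real limit: the claim can only be that the text shown states no extra draw. The point still stands because it rests on a permission that is printed without exception, not on a missing list.

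**The precautions may already be a continuing bar.** The risk section says that patients on these drugs are to be excluded and lists this beside on-treatment measures, so it can be read as applying throughout. No stopping rule carries it out beyond rules 1 and 2, however, and the on-study permission does not reflect it. If a continuing bar was meant, that sentence needs the same amendment.

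**The 2-week figure is only the trial calendar.** This is correct. It is the wait to the next scheduled trial draw under an assumed start time. It is not the wait to any potassium check, since a warned physician may test sooner. Nor is it an event rate. The 1-week interval is set for study drug changes only, so the 74% is a yardstick and not a breach of a protocol rule.

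**Exposure is limited.** Allocation is 1:1, so about half of such starts would be on placebo. Drospirenone users are screened out at entry, and the risk section does not name drospirenone, so only a mid-study change of product remains.

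A reader might infer that the protocol contradicts itself or that these participants go unmonitored. Neither is supported. An entry exclusion and a general permission can coexist, and the scheduled draws and potassium thresholds continue for everyone.

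**Conclusion.** This is a minor participant-safety point and a cheap improvement. The on-study permission does not except the classes barred at entry, and the text shown prompts no trial potassium draw when one is started outside rules 1 and 2. The next scheduled draw is then about 2 weeks away on average (nominal maximum 5 weeks), assuming uniform start times and draws on their nominal dates.

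The documents give no figure for how often such a drug would be started, and none is assumed, so the number of extra hyperkalemia cases cannot be estimated. The hazard is further limited by entry conditions (potassium not above 5 mEq/L, eGFR not below 50), seven scheduled draws, the hold at 5.3 and stop at 6.0 mEq/L, and the warning to the treating physician. The primary analysis is not affected.

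**What to change.** 1. Amend the closing sentence of *Overview of study design and study population* so that the classes in exclusion criterion 10 are to be avoided during treatment.
2. List those classes in the notice already sent to the primary practitioner.
3. In *Participation of pregnant women*, qualify hormonal contraception with the words: other than drospirenone-containing products.
4. If one of these drugs must be started, have it reported to the investigators, check potassium and creatinine within about one week under the existing thresholds, and hold the step to 50 mg until the result is known. Because treatment is blinded, this applies in both arms. Rules 1 and 2 stay as they are.

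Cost: two amended sentences, one list in an existing notice and one short rule, a few extra blood draws, and a few participants held at 25 mg for a short time.

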### Study endpoints

Our primary endpoint is the effect of spironolactone therapy on the change in placebo-corrected 6-minute walk distance at 24 weeks relative to baseline values and the incidence of clinical worsening in the spironolactone group compared to placebo. Clinical worsening will be defined as the addition of a new PAH-specific medication (a prostacyclin, an endothelin-1 receptor antagonist or a phosphodiesterase-5 inhibitor), dose or route escalation (that is inhaled prostacyclin changed to intravenous prostacyclin) of a current PAH-specific medication, development of right heart failure requiring hospitalization or an escalation in outpatient diuretic therapy (that is, initiation of a new diuretic or a dose escalation of current diuretic therapy), transplantation, or death.

Secondary endpoints include effect of spironolactone therapy on exercise capacity, as measured by the change in placebo-corrected VO_2_ maximum at 24 weeks relative to baseline values; effect of spironolactone therapy on plasma markers of vascular inflammation (see Table 2) and peripheral blood mononuclear cell (PBMC) gene expression profiles, comparing changes from baseline between the treatment and placebo groups; effect of spironolactone therapy on sympathetic nervous system activation, renin-angiotensin-aldosterone system activation and sex hormone metabolism, comparing changes from baseline between the treatment and control groups (see Table 2); effect of spironolactone therapy on RV function as assessed by echocardiography, magnetic resonance imaging (MRI) and N-terminal pro-brain natriuretic peptide (NT-proBNP), comparing changes from baseline between the treatment and placebo groups; and safety and tolerability of spironolactone therapy as determined by the rate of study drug discontinuation due to hyperkalemia (serum potassium ≥5.3 mEq/L), renal insufficiency (serum creatinine rise >50% of baseline), or other side effects such as breast pain and gynecomastia compared to placebo.

**Table 2 T2:** Biomarker assessment

**Markers of endothelial dysfunction**	**Neurohormonal axis**
**Adhesion molecules**	**Sympathetic activation**
sICAM-1, sVCAM-1, sE-selectin	Epinephrine, norepinephrine, arginine vasopressin
**Markers of activated coagulation**	**Renin-angiotensin-aldosterone system activation**
von Willebrand factor, thrombomodulin, sP-selectin	Renin activity, aldosterone, angiotensin II, NT-proBNP
**Cytokines and chemokines**	**Sex hormone metabolism**
TNFα, IL-1β, IL-6, IL-7, IL-8, MCP-1, sCD40L, IL1RL1	Androstenedione, dehydroepiandrosterone sulfate, free testosterone, estradiol, 2-methoxyestradiol, urine 2-hydroxyestradiol:16α-hydroxyestrone ratio

Abbreviations: IL-1β, interleukin-1 beta; IL1RL1, interleukin-1 receptor-like 1; IL-6, interleukin-6; IL-7, interleukin-7; IL-8, interleukin-8; MCP-1, monocyte chemotactic protein-1; NT-proBNP, N-terminal pro-brain natriuretic peptide; sCD40L, soluble CD40 ligand; sICAM-1, soluble intercellular adhesion molecule 1; sVCAM-1, soluble vascular cell adhesion molecule 1; TNFα, tumor necrosis factor alpha.

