### Statistical considerations and analysis of the study

#### Sample size

Previous studies have examined the effects of PAH-specific therapy on time to clinical worsening, exercise capacity and endothelial inflammation in patients with PAH [59-63]. Moreover, the effects of spironolactone on endothelial dysfunction have been examined in diverse non-PAH patient populations [19-23]. However, no prior randomized controlled trials have been completed that report on the effects of spironolactone treatment in patients with PAH. Assuming that a subset of the participants with PAH may discontinue study drug or otherwise not be able to complete the study, we plan to enroll up to 70 participants with PAH to obtain at least 50 completed studies. The participants will be randomized in a 1:1 ratio to spironolactone therapy or placebo. At a two-sided α level of 0.05, we will have at least 84% power to detect an effect size (group mean difference divided by standard deviation) of 0.9 for the difference in the change of 6-minute walk distance from baseline between the two treatment groups [61].

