#### Study analysis

Participant characteristics will be summarized using contingency tables (for categorical variables), means and standard deviations for continuous variables that are approximately normally distributed (transformed if needed) or median and inter-quartile range for continuous variables that are not normal.

For the primary endpoints, changes in 6-minute walk distance (24 weeks versus baseline) will be compared between the two groups using linear mixed models (LMMs), Kaplan-Meier curves will be plotted to show the time to clinical worsening, and a log-rank test will be used to compare the two arms. Chi-squared tests or Fisher exact tests, t-tests or Wilcoxon rank-sum tests will be used to compare variables between the two arms when appropriate. The rates of study drug discontinuation between the two arms will be compared using the Fisher exact test, and a logistic regression will be considered to account for potential confounders if the two arms are imbalanced. The causes of discontinuation will be tabulated and compared if appropriate.

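### Two primary outcomes, each with its own test, but no rule for combining them; the only stated alpha and power belong to 6-minute walk distance

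*Protocol article*

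**What the plan says.** Study endpoints opens with 6MWD: "Our primary endpoint is the effect of spironolactone therapy on the change in placebo-corrected 6-minute walk distance at 24 weeks". The same sentence then adds a second outcome, "relative to baseline values and the incidence of clinical worsening in the spironolactone group compared to placebo". The Abstract pairs the two in the same way.

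Study analysis moves to the plural and separates them. For 6MWD: "For the primary endpoints, changes in 6-minute walk distance (24 weeks versus baseline) will be compared between the two groups", by linear mixed models. For the other outcome: "Kaplan-Meier curves will be plotted to show the time to clinical worsening, and a log-rank test will be used to compare the two arms". They are therefore two outcomes with two tests and are not combined into a composite.

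Sample size gives one alpha and one power figure: "At a two-sided α level of 0.05, we will have at least 84% power to detect an effect size". The target is an "effect size (group mean difference divided by standard deviation) of 0.9 for the difference in the change of 6-minute walk distance". Clinical worsening has no assumed event rate, effect size, power or significance level. The only multiplicity control in the article is the false discovery rate used to select genes under Microarray analysis.

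**The concern.** With two primary outcomes and two tests, the reader needs to know what counts as a positive trial: either result, both, or one before the other. Each answer has a different false-positive rate and a different power, and the article does not choose.

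Two things are at stake. First, if the choice is left until the results are known, a favourable result on either outcome could be presented as the primary result, and the chance of a false claim would then exceed 5%. Second, the design was sized on 6MWD only, so under some rules the stated power is not the power of the primary objective.

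**Working it through.** **Inputs from the protocol article.** Two-sided alpha 0.05; standardised difference d = 0.9 for 6MWD change; 1:1 allocation; up to 70 enrolled (35 per arm) to obtain at least 50 completers (25 per arm). All are under Sample size.

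**Inputs that are assumed.** The article gives no event rate or hazard ratio for clinical worsening. I take 24-week placebo rates of 10% to 50% and a hazard ratio of 0.5. A level of 0.05 for the log-rank test is also an assumption.

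**Step 1: reproduce the stated power.** For a two-sample t-test with n per arm, the noncentrality is d × √(n/2) = 0.9 × √12.5 = 3.18, with 48 degrees of freedom and critical value 2.011. Power is 87.7% (88.9% by the normal approximation). The stated floor of 84% is met for 6MWD alone at the full 0.05.

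**Step 2: either outcome can win, each at 0.05.** If the tests are independent, the family-wise error is 1 − 0.95² = 9.75%; the upper bound is 0.05 + 0.05 = 10%. With correlated test statistics (bivariate normal):

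| Correlation | Family-wise error |
|---|---|
| 0 | 9.75% |
| 0.3 | 9.5% |
| 0.5 | 9.1% |
| 0.7 | 8.3% |
| 0.9 | 7.0% |

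**Step 3: alpha split equally, 0.025 each.** Noncentral t power for 6MWD at d = 0.9:

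| Completers per arm | Power at 0.05 | Power at 0.025 |
|---|---|---|
| 25 | 87.7% | 80.4% |
| 27 | 90.1% | 83.8% |
| 28 | 91.1% | 85.2% |
| 35 | 96.0% | 92.7% |

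At the planned minimum the split falls short of 84% by 3.6 points. From 28 completers per arm (56 in all) there is no shortfall.

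**Step 4: both outcomes must win.** The error rate stays at or below 5%, but joint power cannot exceed log-rank power. With placebo rate p and hazard ratio 0.5, the spironolactone rate is 1 − (1 − p)^0.5. With 35 per arm, expected events are D = 35 × (sum of the two rates). By Schoenfeld's formula, power = Φ(√D/2 × ln 2 − 1.96).

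| Placebo rate (assumed) | Spironolactone rate | Events D | Log-rank power |
|---|---|---|---|
| 10% | 5.1% | 5.3 | 12% |
| 20% | 10.6% | 10.7 | 20% |
| 30% | 16.3% | 16.2 | 29% |
| 40% | 22.5% | 21.9 | 37% |
| 50% | 29.3% | 27.8 | 45% |

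Following all 70 participants favours the design. With 50 participants the 10% to 40% rows fall to about 10% to 28%.

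**Step 5: fixed sequence, 6MWD first.** 6MWD is tested at 0.05, and clinical worsening is tested at 0.05 only if 6MWD is significant. The family-wise error is at most 5% and 6MWD power stays as in Step 1. Of the rules considered here, this is the one that keeps both stated figures, but the article does not state it.

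**The case against.** The strongest reply is that this is an absence rather than an error. The article condenses a fuller protocol, and an analysis plan not shown may set the order. Sizing the trial on 6MWD fits its being the lead endpoint, and nothing in the article contradicts a fixed sequence that starts there. This stands in part: the article does not exclude a sound rule. Even so, it declares two primary outcomes itself, assigns each a test and attaches all alpha and power to one. A later plan that split alpha equally would undercut the stated power at 50 completers, and one requiring both would leave the primary objective without a stated power.

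Two stronger readings are tempting, and the document supports neither.

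- A reader might infer that each outcome is tested at the full 5%, so that the trial has a 10% error rate. No level is written beside the log-rank test and no success rule is given. The 7% to 10% is conditional on the either-wins rule, and its top end needs near-independence, although the two outcomes plausibly move together.
- A reader might infer that the 84% is wrong or does not apply. Sample size and the Abstract both tie it to 6MWD change, for which it is correct. It is never claimed for a joint objective.

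The pilot label, used under Protocol stopping rules and in the Discussion, lowers the consequence. It does not say which outcome decides the result. The clinical worsening definition is also broad, since it counts any dose escalation of PAH-specific or outpatient diuretic therapy, so event rates could be high. That is why the assumed range runs to 50%; power there is still only 45%.

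**Conclusion.** The point holds in a limited form: two primary outcomes are named and separately tested, with no rule for combining them, and only 6MWD is powered. What follows depends on the rule chosen:

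- **Either wins:** family-wise error of about 7% to 10%, assuming 0.05 for the log-rank test and correlation between 0 and 0.9.
- **Equal split:** the stated power is missed only near the completer minimum.
- **Both must win:** power of at most about 12% to 45% with 35 per arm, resting wholly on the assumed event rates and hazard ratio of 0.5.

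The 84% itself needs no correction. Severity is moderate: the rule for success on the primary outcomes is open, but the trial is described as a pilot and the repair is simple.

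**What to change.** Name 24-week change in 6MWD as the sole, or first-tested, primary endpoint at two-sided 0.05. Test clinical worsening second in fixed sequence, at two-sided 0.05, only if 6MWD is significant; otherwise report its estimate and confidence interval descriptively. State in Sample size that clinical worsening is not powered. An alpha split or a both-must-win rule would also be valid, but the power would then have to be restated to match.

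The change is to wording in the Abstract, Study endpoints, Sample size and Study analysis. It adds no participants and leaves 6MWD power as stated. The cost is that no confirmatory claim on clinical worsening is possible if 6MWD fails. The article reports the trial as still recruiting, so the rule should be fixed before any unblinded comparison of the arms.
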